### Statistical analyses

All data analysis will be carried out according to a pre-established analysis plan. The primary analysis will be intention-to-treat. Two sided significance tests will be used. Power calculations will be conducted on all parametric analyses. Only findings with power > 80%, CI = 95% and ά < 0.05 will be determined to be statistically significant. Differences between the intervention and comparison groups in the proportion of mothers using nursing, medical, other health, parental support and child care services will be analysed using contingency tables. Descriptive analyses will be undertaken of critical events such as death or child removal as the incidence of these events is low in the Australian population. Impact and outcome data collected at multiple time points will allow imputation of missing data for participants who did not complete every data point using appropriate techniques [24,25]. Child development and parent-child interaction measures, and quality of the home environment (HOME inventory) will be analysed cross-sectionally at each collection point. All other impact and outcomes measures will be analysed cross-sectionally at 1, 12 and 24 months, to estimate the prevalence of each impact and outcome, their association with demographic and risk factors, and differences between the intervention and comparison groups using contingency tables for non-parametric data and t-tests for parametric data. Longitudinal analyses will then be undertaken to compare differences in outcomes over time between the intervention and comparison groups using Repeated Measures ANOVA for parametric data and Friedmans two-way ANOVA for non-parametric data.

A priori subgroup analyses will be conducted using General Linear Modelling to assess differences between the intervention and comparison groups in impact and outcomes for: first-time mothers compared with mothers with two or more children; Australian born mothers compared with mothers born overseas; mothers with only one risk factor compared with mothers with multiple risks at the time of recruitment antenatally; and mothers with lower psychosocial resources due to probable distress at the time of recruitment (EDS score of 10 or more) compared with mothers with higher psychosocial resources for parenting (EDS score of 9 or less).

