**Figure 3 F3:**
[figure not shown]
**Rate of active follow-up by main source of household income at time of study recruitment**.

Women who booked in to receive their antenatal care after 20 weeks gestation were significantly more likely to be lost to follow-up at every point from 18 months follow-up onward than women who received their antenatal care before 20 weeks pregnant (see Figure 4: 18 month χ^2^_1 _= 6.8 p = 0.01; 24 month χ^2^_1 _= 10.7 p = 0.002; 30 month χ^2^_1 _= 10.9 p = 0.001). Women who reported being abused themselves as a child were significantly less likely to be lost to follow-up at every point from 18 months follow-up onward than women who were not abused themselves as children (see Figure 5: 18 month χ^2^_1 _= 5.3 p = 0.02; 24 month χ^2^_1 _= 4.4 p = 0.05; 30 month χ^2^_1 _= 5.0 p = 0.03). These differences were apparent in both the intervention and comparison groups. There were no other differential rates of attrition according to any demographic or risk factors for either the intervention or comparison groups.

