## Discussion

This study, the first Australian study to measure the impact of a SNHV program commencing antenatally, continuing to child-age 2 years, successfully recruited a cohort of women at-risk of poorer parenting outcomes from a disadvantaged community. The number of women to participate in the study was limited to the maximum caseload of the intervention nurses and a matching number of comparison women. Rates of retention were poorer than predicted, with 62.5 percent retained at 30 months. The rates of retention at 12 and 24 months (86% and 74% respectively), however, compare somewhat favourably with those reported in previous randomised control trials [12], which had a mean retention rate of 84 percent for studies measuring outcomes up to 12 months and 77 percent for studies measuring outcomes up to 24 months.

The rates of participation of women in data collection at each data point, however, ranged from 67.7 percent at 1 month postnatal to 51.4 percent at 24 months postnatal. Participation by the intervention group was more complete than the comparison group, with the comparison group having lower participation at each data point, despite similar rates of active follow-up. Importantly, however, retention and participation rates were not significantly different for the intervention and comparison groups at any time point, and hospital clinical and community service use data will be available for the whole cohort.

Women who presented for antenatal care after 20 weeks pregnancy were particularly difficult to retain in the study, and this may be indicative of a group that is difficult to engage in service delivery and hence also service based research. There is evidence that women with other risk factors, including those with multiple risks or higher particular risks, such as domestic violence or drug or alcohol use, were retained at the same rate as their relatively lower risk counterparts, with one group of women, those who were abused themselves as children, more likely to participate throughout the study than women who were not abused.

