A particular strength of the study was recruitment of women through the public hospital antenatal clinic, using a population base for recruitment. In NSW most women (74.4%) utilise the public hospital for birthing services [31], and the proportion is likely to be higher for women in disadvantaged communities. There is evidence that home visiting interventions that are based in population level recruitment are more likely to be successful than those based on referral of clients [32]. Further, the intervention was based in the local primary health care service and utilised resources and infrastructure available in the local area rather than using a separate, specialised research-based team, making this a trial of a program that is directly replicable at the service level.

Women whose lack of English-language proficiency required the use of an interpreter were excluded from the study, and this may limit the generalisability of the study. The study did, however, include a large proportion of women from non-English speaking backgrounds, facilitated by the use of interviewer administered questionnaires that required only English language ability that is sufficient to understand simple verbal questions, rather than English language proficiency or literacy.

The most significant limitation of the study is the low rates of participation at each data point, which may reduce the power of the study to detect small and moderate effects of the intervention. The collection of the same data items at multiple data points should facilitate imputation of values for data points missed by individual participants and minimise the impact of lower participation, however, this will remain a limitation for measures analysed cross-sectionally.

The MECSH trial has been designed to provide Australian evidence of effective intervention to improve the health and development of children living in disadvantaged communities who are at-risk of poorer outcomes. It is envisaged that the comprehensive ecological base of the intervention and research measures, and the location of the trial within existing local services, will provide evidence of best practice to reduce inequalities through early childhood intervention.

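### HOME, child development and parent-child interaction appear to get available-case tests at each visit, unadjusted for known predictors of loss, which sits badly with the intention-to-treat statement

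*Protocol article*

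**What the plan says.** The Statistical analyses section of the protocol article makes four statements that bear on this point.

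- On principle: "The primary analysis will be intention-to-treat".
- On missing data: "Impact and outcome data collected at multiple time points will allow imputation of missing data for participants who did not complete every data point".
- Directly after that, on three outcomes: "Child development and parent-child interaction measures, and quality of the home environment (HOME inventory) will be analysed cross-sectionally at each collection point". No adjustment for predictors of loss is stated for them.
- All other outcomes are also tested cross-sectionally first, at 1, 12 and 24 months. Then: "Longitudinal analyses will then be undertaken to compare differences in outcomes over time between the intervention and comparison groups", by Repeated Measures ANOVA or Friedman's test. The outcomes that this second step covers are not listed.

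The Discussion returns to missing data. Repeated collection should help imputation, but of low participation it says that "this will remain a limitation for measures analysed cross-sectionally". It reports that participation "ranged from 67.7 percent at 1 month postnatal to 51.4 percent at 24 months postnatal".

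Retention and Participation reports who was lost. Women booking after 20 weeks were "significantly more likely to be lost to follow-up at every point from 18 months follow-up onward". Women with full-time household income were lost less often at 18 and 24 months, and women abused as children were lost less often from 18 months on. These patterns appeared in both arms. Loss and participation did not differ significantly by arm, although the Discussion notes lower participation in the comparison arm at every point.

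**The concern.** HOME and the Bayley mental scale are two of the three continuous outcomes named in the Sample size section. Read together, the Statistical analyses section and the Discussion suggest that the missing-data remedy does little for the outcomes labelled cross-sectional. A visit-by-visit test on the women seen would then ignore what is known about absent women from their other visits and from baseline.

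This looks avoidable. Under Data collection, developmental assessment and interaction were observed at about 18 and 30 months, and the antenatal, 12-month and 24-month interviews included observation measures. The three factors shown to predict loss were all recorded at recruitment.

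At stake is power first, since the plan calls a finding significant only if its power also exceeds 80%. Next is whether the result describes the randomised cohort or its easier-to-retain part. Last, under further conditions, is bias in the arm contrast.

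**Working it through.** **Inputs.** 75 per group, power 0.80, effect size 0.5, planned recruitment 90 per group, 15% loss (Sample size). Two-sided testing at 0.05 (Statistical analyses). Randomised 111 and 97 (Sample Description). Participation 67.7% at 1 month and 51.4% at 24 months (Discussion); the Abstract gives 66% and 51%. Active follow-up 86%, 74% and 63% at 12, 24 and 30 months (Abstract).

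**1. The plan's own figures.**
- Recruitment: 75 / (1 − 0.15) = 88.2, so 89 per group, against 90 stated. This agrees closely.
- Power at 75 per group: SE = √(2/75) = 0.163 SD; 0.5/0.163 − 1.96 = 1.10; power = Φ(1.10) = 0.865 (0.860 by t-test).
- For 0.80, n = 2 × (1.96 + 0.84)² / 0.5² = 63 per group.

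The stated 0.80 is therefore true as a conservative bound.

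**2. Power if only women seen at 24 months are analysed.** Equal participation by arm is assumed, because the text gives no rates by arm.
- 0.514 × 111 = 57.1; 0.514 × 97 = 49.9; total about 107.
- SE = √(1/57.1 + 1/49.9) = 0.194.
- Power for 0.5: Φ(0.5/0.194 − 1.96) = Φ(0.62) = 0.73 (0.72 by t-test).
- Effect detectable with 80% power: 2.80 × 0.194 = 0.54.

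| Women analysed | Power for 0.5 | Detectable effect |
|---|---|---|
| 208 (all, no information lost) | 0.95 | 0.39 |
| 141 (67.7%, 1 month, Discussion) | 0.84 | 0.47 |
| 137 (66%, 1 month, Abstract) | 0.83 | 0.48 |
| 131 (63%, all in active follow-up at 30 months tested: an upper limit) | 0.81 | 0.49 |
| 107 (51.4%, 24 months) | 0.73 | 0.54 |

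A model on all visits, or imputation, would fall between the 24-month row and the top row. Where it falls depends on within-woman correlations, which the article does not give.

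**3. What a 24-month test leaves out.** Active follow-up was 0.74 × 208 = 154 women and participation 107, a gap of about 47. By the caption of Figure 2, women in active follow-up who missed that point had completed the previous point or completed a later one. The neighbouring points are the 18- and 30-month assessments. For HOME itself the useful earlier value would come from another interview, and its schedule is in a figure not shown.

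**4. How strongly loss depends on baseline.** Late bookers number 42 + 35 = 77 and the others 131. Solving χ² = d² × (77 × 131/208) / [p(1 − p)] for the difference d:
- 24 months, χ² = 10.7, p = 0.74: d = 0.206, about 61% against 82%.
- 30 months, χ² = 10.9, p = 0.625: d = 0.230, about 48% against 71%.

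This assumes all 208 women and uncorrected chi-squares. These are rates of active follow-up, not of data availability at a visit.

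**5. When this biases the arm contrast.** An illustrative simulation on assumed values: a baseline factor in 37% of women, worth −0.5 SD; participation 60% without it and 36% with it; true effect 0.50.
- Same loss in both arms, no effect modification: unadjusted estimate 0.50.
- Effect modification of ±0.4 SD, same loss in both arms: 0.46 to 0.54.
- Participation differing by 15 points between arms among women with the factor, no effect modification: 0.465 or 0.545, by direction.
- Both together: 0.45 to 0.62. With lower participation in the comparison arm, the direction reported, 0.45 to 0.48; the 0.62 arises in the opposite direction.
- A model with the factor and its interaction with arm: 0.50 to two decimals in every case.

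**The case against.** A reader might infer that the trial will run a completer analysis on 51% of its sample under an intention-to-treat label. The article does not support that.

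- The imputation sentence stands immediately before the cross-sectional one. Nothing there restricts the three outcomes to women seen; a cross-sectional test can use imputed values, and all other outcomes are first tested cross-sectionally too.
- Without imputation, the tests would be available-case at each visit, with mothers kept in their randomised arms. A woman seen at 18 but not 30 months would still count at 18.
- The 51% belongs to 24 months. It can apply to HOME if HOME was taken then, but not to assessments at 18 and 30 months.
- Comparing arms among those seen does not require data missing completely at random. Loss that depends on baseline and is alike in both arms leaves the contrast unbiased unless the effect varies with the same factors. The article reports the predictors in both arms and no significant arm difference.
- Repeated Measures ANOVA would be held to at most 107 women over 1, 12 and 24 months only without imputation, which the plan foresees.
- Details of imputation may sit in the analysis plan that the article mentions.

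All of this stands. It limits the point without removing it. The article chooses a method for these outcomes and itself says that low participation will remain a limitation for cross-sectional measures, so this is more than silence left to another document. An arm difference that is not significant, with about 100 women per arm, does not show equal participation.

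**Conclusion.** The concern holds in a limited form. The article leaves unclear whether imputation reaches HOME, development and interaction, and its Discussion points against much help for them. On the natural reading they receive unadjusted available-case tests, which fit poorly with the intention-to-treat statement.

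The size can be given only for 24 months: power of about 0.73 for an effect size of 0.5, against the stated 0.80, and a detectable effect of 0.54. This assumes that HOME was taken then, that participation was equal by arm and that nothing is imputed. For development and interaction no figure can be given, because participation at 18 and 30 months is not in the text.

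The more certain costs are power and generalisability. Bias in the arm contrast is possible, but needs effect modification, or differential or outcome-dependent loss. The article shows none of these; lower comparison-arm participation is a reason for care.

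**What to change.** - For each outcome measured more than once, estimate the visit-specific arm contrast from a likelihood-based mixed model on all available visits (arm, visit, arm-by-visit), or from multiple imputation done by arm. Include late booking, income source, childhood abuse and the baseline value where one exists.
- Imputing by arm allows the effect to vary with these factors. A mixed model does so only if it has arm-by-factor terms averaged over the cohort, as in the simulation.
- State that this covers HOME, child development and parent-child interaction.
- Use it in place of Repeated Measures ANOVA for parametric outcomes.
- Keep the available-case cross-sectional tests as sensitivity analyses.
- Reconcile the two figures for 1-month participation (66% and 67.7%).

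The cost is analysis-plan wording and modest analyst time. The predictors of loss were recorded at recruitment, so no new data are needed. The downside is reliance on a missing-at-random assumption. The gain in precision cannot be promised in advance, because it depends on correlations that the article does not report.

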### Recruitment

Promotional material was made available through the administration services at the time of booking into the hospital for confinement and posters were displayed in the hospital antenatal clinic waiting room. Eligible participants were identified by the Senior Research Officer (SRO) who was provided daily with the records of all new bookings. Details of eligible women were entered onto a database, and were crosschecked with antenatal clinic staff at a weekly meeting to ensure that processes of recruitment to the trial did not adversely affect clinical referral processes for at-risk women. Once cleared for contact regarding the trial, the Research Assistant (RA) made the initial approach by telephone to potential participants, provided brief information and sought permission to visit the pregnant woman at home. Informed consent was not sought at this point.

The RA subsequently visited women who had given verbal permission in their homes, provided detailed information about the study, including the advice that they may or may not receive a home visiting intervention, and obtained the women's informed written consent. Once consent was obtained, the RA administered the antenatal baseline questionnaire. After baseline measures were completed, women were given a sealed envelope that contained information advising them of their group assignment. Once consent forms and baseline data were returned to the SRO, the intervention team was advised of the names and contact details of consenting women randomised to receive the MECSH intervention. Consenting mothers allocated to the comparison group and those who did not consent to participate were reassured that they would receive usual care.

One month after the children were born, and at 6, 12, 18, and 24 months postpartum, all participants were re-contacted by the RA. At each point verbal consent was obtained to visit the mother at home, to administer questionnaires and conduct observations. Records were kept of acceptance and attrition rates to allow later 'intention to treat' analyses.

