**Figure 1 F1:**
[figure not shown]
**Measurements**.

Study measures were obtained by interviewer administered questionnaire antenatally and at 1, 12, and 24 months postpartum. In addition, women were telephoned at 6 months postpartum to maintain contact and encourage study retention. Antenatal, 12 month and 24 month questionnaires were administered by face-to-face interview and included observation measures. Interviewer administration was chosen due to low literacy rates within the study population. At approximately 18 and 30 months standardised developmental assessments and observation of parent-child interaction were conducted and videotaped either at the hospital, community health facility or the family home. All questionnaires and standardised testing were administered in English.

With consent, hospital clinical and community service use data were obtained for the mother and her child from the hospital inpatient and outpatient records and community health records for the period from birth up to 24 months postpartum. These data are available for the whole sample and is not dependent on participant retention.

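### Continuous outcomes are compared by unadjusted t-tests although antenatal measures were taken before allocation was revealed; adjustment would gain precision, by an amount the article does not allow to be fixed

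*Protocol article*

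**What the plan says.** The Statistical analyses section treats two classes of outcome differently.

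- For the first class it names no test: "Child development and parent-child interaction measures, and quality of the home environment (HOME inventory) will be analysed cross-sectionally at each collection point".
- For the rest, "All other impact and outcomes measures will be analysed cross-sectionally at 1, 12 and 24 months". Group differences are then tested with "contingency tables for non-parametric data and t-tests for parametric data". No covariate is mentioned.

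Longitudinal comparisons follow, "using Repeated Measures ANOVA for parametric data and Friedmans two-way ANOVA for non-parametric data"; whether the antenatal wave enters them is not stated. General Linear Modelling appears only for the subgroup analyses.

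On baseline data, the Data collection section says: "Study measures were obtained by interviewer administered questionnaire antenatally and at 1, 12, and 24 months postpartum". The Recruitment section gives the order of events: "Once consent was obtained, the RA administered the antenatal baseline questionnaire", and then "After baseline measures were completed, women were given a sealed envelope that contained information advising them of their group assignment". The Study Design section adds that the EDS was used in the antenatal clinic as part of the eligibility assessment.

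**The concern.** A two-sample t-test makes no use of what was known about each woman before she learned her group. Where the same measure was taken in pregnancy and again later, the antenatal value usually explains part of the later variation. ANCOVA removes that part from the error term, at no cost in new data.

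This matters because the Discussion names low participation as the study's main limitation, on grounds of power. It expects imputation to help, but concedes that the problem stays for measures analysed cross-sectionally. The t-tests are cross-sectional analyses.

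**Working it through.** **Inputs from the article.** 208 women were randomised, 111 to intervention and 97 to comparison (Sample Description). Participation at 24 months was 51.4% (Discussion). The design is 75 per group, power 0.80, standardised effect d = 0.5 (Sample size), with two-sided tests at 0.05 (Statistical analyses).

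**Assumed inputs.** The baseline-outcome correlation r is not given, so a range is shown. Participants at 24 months are split in proportion to allocation. The Discussion says the comparison group took part less at each point, so the true split may differ.

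**The plan's own figure.** With 75 per group and d = 0.5, power is 0.865 (normal) or 0.860 (noncentral t), not 0.80. Power of 0.80 needs 63 to 64 per group, and 75 per group reaches it at d = 0.46. The stated 0.80 for effects of 0.5 or larger is therefore a conservative bound. The recruitment target agrees: 75/(1 − 0.15) = 88.2, so 89, against 90 planned.

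**Unadjusted comparison at 24 months.**
- Participants: 0.514 × 208 = 106.9, or about 57 and 50.
- Standard error in SD units: √(1/57.05 + 1/49.86) = 0.194.
- Power: Φ(0.5/0.194 − 1.96) = 0.73 (noncentral t: 0.72).
- Effect detectable with 80% power: (1.96 + 0.84) × 0.194 = 0.54.

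**With adjustment for the antenatal value.** The residual SD is √(1 − r²), and the effective sample is 106.9/(1 − r²). Recovery is the gain in effective sample divided by 150 − 106.9 = 43.1 (design shortfall) or 208 − 106.9 = 101.1 (loss from randomised).

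| r (assumed) | Power, d = 0.5 | Detectable d | Effective N | Recovered towards 150 | Recovered towards 208 |
|---|---|---|---|---|---|
| 0 | 0.73 | 0.54 | 107 | – | – |
| 0.3 | 0.77 | 0.52 | 118 | 25% | 10% |
| 0.4 | 0.80 | 0.50 | 127 | 47% | 20% |
| 0.5 | 0.85 | 0.47 | 143 | 83% | 35% |

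Half the gap to 150 needs r of about 0.41 and all of it about 0.54. Half the loss from 208 needs about 0.57.

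**Which outcomes this reaches.**
- Of the three continuous measures in the sample size statement (HOME, Bayley, SF-12), only SF-12 falls under the t-test clause.
- Developmental testing cannot have an antenatal value: "At approximately 18 and 30 months standardised developmental assessments and observation of parent-child interaction were conducted". Parent-child interaction, immunisation, child injury and breast-feeding have none either.
- EDS has a booking value. Which other measures were taken antenatally is in Figure 1, which is not reproduced in the text reviewed.
- The variance formula is for continuous outcomes and does not carry over to logistic regression.

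**Baseline imbalance.** First-time mothers: 31/111 (27.9%) against 34/97 (35.1%), p about 0.27. Domestic violence: 10/111 (9.0%) against 4/97 (4.1%), p about 0.16 to 0.18. The mean number of risks is 1.7 in both groups. These differences are within chance.

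**The case against.** The strongest reply is that nothing here is an error. After randomisation an unadjusted t-test is valid, and the choice is one of efficiency. The article refers to a pre-established analysis plan that may add covariates. It also plans repeated-measures analyses and imputation, either of which might draw on the antenatal wave. If everyone in active follow-up at 24 months (74%, about 154 women) had data, unadjusted power would already be 0.87.

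Most of this stands as a limit on the point, but it does not remove it. The article names the test, so this is not a detail merely left to another document. The repeated-measures analysis comes after the t-tests and does not replace them, and the text does not say that it uses the antenatal wave. Active follow-up is not data: 51.4% took part at 24 months, and imputed values do not carry the information of observed ones.

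Three stronger readings are tempting and are not supported.

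- A reader might infer that adjustment would make good much of the attrition. That needs r of roughly 0.4 to 0.6 between pregnancy and 24 months, and the article gives no correlation.
- A reader might infer that baseline data serve only to describe the sample and form subgroups. The plan also examines associations of outcomes with demographic and risk factors, although those are not adjusted group comparisons.
- A reader might infer that the baseline imbalances distort the result. They are compatible with chance, and the article does not show that either factor predicts the outcomes.

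**Conclusion.** The point holds as one of avoidable inefficiency, for continuous outcomes covered by the t-test clause that have an antenatal value of the same measure. At 24 months, power for d = 0.5 would rise from about 0.73 to between 0.77 and 0.85 for r from 0.3 to 0.5. This rests on the assumed correlation, on a proportional split of about 107 participants, and on analysis of participants without imputation. A less even split would lower every power figure somewhat, but would leave the relative gain in effective sample unchanged.

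For outcomes with no antenatal value, the gain from other prognostic covariates is unknown and probably smaller. Adjustment sharpens the estimate among those observed. It does not supply missing data, and by itself it does not remove bias from the uneven loss by income source, timing of antenatal care and childhood abuse that the article reports.

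**What to change.** In the Statistical analyses section, replace the t-test with ANCOVA, or a mixed model, for the group comparison of continuous outcomes, adjusting for the antenatal value of the same measure wherever one exists (EDS, and any others listed in Figure 1). For outcomes without one, a short covariate list may be used, for example parity and EDS at booking. Parity is complete in Table 1, since 31 + 80 = 111 and 34 + 63 = 97; level of education is not. The same passage should name the test for child development, parent-child interaction and HOME, so that it is clear whether the adjustment applies to them.

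The cost is analysis-plan wording. The article describes the analysis as still to come, and no new data are needed. The covariate list must be fixed before outcome data are analysed.

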## Methods and design

The overarching hypothesis of the trial was that children born to at-risk mothers receiving SNHV will have significantly better environmental, child, maternal and family outcomes than those receiving usual care.

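### Repeated Measures ANOVA makes poor use of the antenatal value; a baseline-adjusted average over the post-birth visits would give more power from the same data

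*Protocol article*

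**What the plan says.** The hypothesis, at the start of Methods and design, concerns the level of outcomes: "children born to at-risk mothers receiving SNHV will have significantly better environmental, child, maternal and family outcomes than those receiving usual care".

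Under Data collection, the article states that "Study measures were obtained by interviewer administered questionnaire antenatally and at 1, 12, and 24 months postpartum". Under Recruitment, the baseline questionnaire is completed before the woman learns her group, so an antenatal value cannot carry a programme effect.

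Statistical analyses sets out two steps.

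- **Visit by visit.** "All other impact and outcomes measures will be analysed cross-sectionally at 1, 12 and 24 months", with "differences between the intervention and comparison groups using contingency tables for non-parametric data and t-tests for parametric data". For the child development, parent-child interaction and home environment measures, the wording is that "quality of the home environment (HOME inventory) will be analysed cross-sectionally at each collection point". "Two sided significance tests will be used".
- **Longitudinal.** This step follows the first, and its purpose and method are given as: "compare differences in outcomes over time between the intervention and comparison groups using Repeated Measures ANOVA for parametric data".

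The longitudinal sentence does not say whether the group main effect or the group-by-time interaction is the test. It does not say whether the antenatal measurement is one of the repeated occasions, and it names no covariate.

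**The concern.** Repeated measurement should sharpen the comparison of the two groups. It does so only if the baseline value is used to explain variation between women. The named method has no natural place for a baseline other than as one more time point, where no treatment effect is possible. A main effect that averages over that time point is pulled towards zero. An interaction that includes it spreads the test over three degrees of freedom. If the antenatal value is left out, what it predicts about later scores stays in the error term.

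This matters here because the Discussion names low participation, and the power it may cost, as the trial's most significant limitation, and looks to the repeated data items to soften the loss.

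**Working it through.** **Plan's own figure.** Sample size states power 0.80 with 75 per group at an effect of 0.5 SD. A two-sided 5% comparison gives 0.86, and 0.80 is reached at 0.46 SD. The stated figure is conservative and does not affect this point.

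**Inputs.** From the article: 75 per group, two-sided 5%, one antenatal and three post-birth visits. Assumed: SD 1 at every visit, equal correlation r between any two visits, and a benefit d that is constant at 1, 12 and 24 months and zero antenatally. The article gives no correlations, so r is taken as 0.5 and then varied. The illustration uses d = 0.3; d = 0.5 follows below.

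**Formula.** For a contrast with mean difference D and per-woman variance V, SE = √(2V/75) and power ≈ Φ(D/SE − 1.96).

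1. *Group main effect, antenatal value as a fourth level.* D = (0 + 0.3 + 0.3 + 0.3)/4 = 0.225. V = (1 + 3r)/4 = 0.625. SE = 0.129, D/SE = 1.74, power 0.41. The factor of 3/4 is the dilution; at d = 0.5 it gives 0.375.
2. *Group-by-time, same four levels.* The squared deviations of the group differences sum to 0.225² + 3 × 0.075² = 0.0675. Noncentrality = (75/2) × 0.0675/(1 − r) = 5.06. With F on 3 and 444 degrees of freedom, power is 0.44.
3. *Group main effect over the three post-birth visits, unadjusted.* D = 0.3. V = (1 + 2r)/3 = 0.667. SE = 0.133, D/SE = 2.25, power 0.61.
4. *Post-birth average adjusted for the antenatal value.* D = 0.3. V = (1 + 2r)/3 − r² = 0.417. SE = 0.105, D/SE = 2.85, power 0.81.

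Required numbers scale with V/D². Relative to option 4, option 3 needs 0.667/0.417 = 1.6 times as many women. Option 1 needs (0.625/0.225²)/(0.417/0.3²) = 2.7 times as many.

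**Range over the assumed correlation (d = 0.3, 75 per group).**

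| r | Main effect, 4 levels | Group-by-time, 4 levels | Post-birth main effect | Adjusted post-birth average |
|---|---|---|---|---|
| 0.3 | 0.52 | 0.32 | 0.71 | 0.79 |
| 0.5 | 0.41 | 0.44 | 0.61 | 0.81 |
| 0.7 | 0.35 | 0.68 | 0.54 | 0.91 |

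The adjusted average is highest in every row. Over the unadjusted post-birth main effect, the gain is small at r = 0.3 (0.71 to 0.79) and large at r = 0.7 (0.54 to 0.91).

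**Larger effect, fewer women.** The Discussion gives 51.4% participation at 24 months. Spread evenly over the groups (an assumption), 51.4% of 208 is 107 women, or 57 and 50. With d = 0.5 and r = 0.5, the four options give about 0.68, 0.75, 0.88 and 0.98.

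**Is a sustained benefit missed?** In simulation with d = 0.5, 75 per group and r from 0.3 to 0.7, using post-birth visits only, the group-by-time test rejects in 5–6% of runs. The group main effect of the same ANOVA rejects in 93–99%, and each visit's t-test in about 85–87%.

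**The case against.** A reader might infer that the longitudinal analysis would report a real, sustained benefit as no difference, because the wording suggests the group-by-time term and that term tests only whether the profiles are parallel. The document does not support this. It never makes the interaction the deciding test and does not exclude the group main effect, which over the post-birth visits detects such a benefit well. The preceding sentence already plans direct comparisons at 1, 12 and 24 months. A null interaction beside significant visit-wise differences would correctly describe a constant effect. If the antenatal value is one of the occasions, the profiles are not parallel and the interaction has power too.

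A second objection is that the term, the occasions and the handling of baseline belong in the pre-established analysis plan, which is not shown. That disposes of any complaint that these details are missing. That plan may also add a covariate. But the method itself is stated in the article, and naming a term does not remove the loss: each of the three ways of reading plain Repeated Measures ANOVA has less power than the adjusted average in the scenarios computed.

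A third objection is that choosing a less efficient model is not an error. That stands, and it sets the weight of the point: this is an improvement, not a correction of something invalid. The advantage over the interaction is also slight when the effect is 0.5 SD and the correlation 0.7, where the interaction already reaches 0.99 with 75 per group.

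**Conclusion.** The point holds as one of efficiency. For continuous measures with an antenatal value, Repeated Measures ANOVA as stated gives away power whichever term or set of visits is chosen. In the central case the loss is from about 0.81 to between 0.41 and 0.61.

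This rests on an assumed 0.3 SD constant benefit, equal correlations of 0.5, complete data on 75 per group, and a linear relation between antenatal and later scores. The size of the gain depends on the correlation. Which continuous measures were taken both antenatally and after birth is set out in the article's Figure 1, which could not be seen for this review. Measures that exist only after birth gain nothing from the covariate; for them the group main effect is already adequate. The validity of the planned tests is not in question.

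**What to change.** Replace Repeated Measures ANOVA for continuous outcomes with a linear mixed model of the 1-, 12- and 24-month values. Include arm, visit and arm-by-visit, and add the antenatal value as a covariate where one exists, not as a repeated level. Take the arm effect averaged over the post-birth visits as the longitudinal test of the programme. Report arm-by-visit as a secondary result on whether the effect grows or fades. Keep the planned visit-wise comparisons.

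The cost is a change of wording in the analysis plan and a different procedure; no new data are needed. The one downside is that an average is less sensitive to a benefit that appears only at 24 months. The retained 24-month comparison covers that case.
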